#### *2. Clinical variables*

As a clinical safety monitoring the following examinations will be performed:

- A complete medical history will be taken at enrollment (screening visit).
- Physical examination will be performed at screening visit and at the end of the treatment period (week 12).

Any evaluations that are abnormal and considered to be related to the study medication will be followed until they return to baseline or are judged not to be clinically significant.

### **Concomitant illnesses**

Other illnesses present at entry to the study are regarded as con­comitant illnesses and will be documented on the case record form pro­vided. Any concomitant illness such as diabetes, hypertension, heart failure etc. should be controlled before entry into the study by appropriate medication which should, if possible, not be changed during the entire study period.

Concomitant illnesses, relevant medication and any changes in concomitant disorders and/or medication have to be documented appropriately in the case record form (CRF).

Illnesses occurring during the study period are to be regarded as adverse events and will each be documented on a separate "Adverse event" page in the case record form. Application of study medication may be continued during intercurrent illnesses, if clinically justifiable.

### **Concomitant treatment**

All treatments being taken by the patients on entry to the study and all treatments given in addition to the study treatment during the study are regarded as concomitant treatments and must be docu­­mented on the case record form, as mentioned before.

The following concomitant treatments (for psoriatic arthritis) are permitted during this study, provided that the patients have received a stable dose for at least 28 days before entering the study:

- nonsteroidal anti-inflammatory drugs (NSAIDs) including acetylsalicylic acid
- oral corticosteroids, if not exceeding a prednisone equivalent of 10 mg daily
- methotrexate

The following concomitant treatments are not permitted during this study (see exclusion criteria):

- intra-articular corticosteroid injections
- oral steroids, if exceeding a prednisone equivalent of 10 mg daily
- DMARDs other than methotrexate
- topical corticosteroids, vit.D analogues, topical retinoids, keratolytics or coal tar (other than on the scalp, palms, groin, and/or soles of feet).

It is important that steroid treatment be kept to a minimum. Changes of NSAIDs and increases in steroid therapy (drug or dosing) should be avoided. If there is a clear reason to do so, the reason and the changes have to be documented in detail in the case record form.

If therapy for pain relief becomes necessary throughout the study, acetaminophen should be used and has to be documented in detail in the case record form. No pain medication should be used within 6 hours prior to joint examination or arthroscopy. Opiates should be avoided.

Patients requiring surgical procedures involving local or regional anesthesia may continue with study medication. Surgical procedures involving general anesthesia should preferably be postponed until the end of the study, if possible. Should patients require (major) surgery involving general anesthesia during the 12-week study period, study medication will be stopped an patients are withdrawn from the study.

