### Inclusion criteria

1. Prior to any study procedure, voluntary written informed consent must be obtained, after the nature and purpose of this study are explained
2. Patients should be between 18 and 80 years of age
3. Patients have presence of active cutaneous lesions of psoriasis or documented history of psoriasis diagnosed by a dermatologist
4. Patients must have a diagnosis of psoriatic arthritis for at least 3 months. The disease must be moderate to severely active as defined by  2 swollen and  2 tender or painful joints
5. If female, patient should either be of not-childbearing potential (i.e. postmenopausal or surgically sterile) or practice a reliable method of birth control until 150 days post-study (e.g. use of condom, IUD, oral contraceptives) or have a vasectomized partner
6. Patients should have inadequate response to NSAID therapy
7. The use of concomitant NSAIDs and corticosteroids is allowed. The dose of corticosteroids should not exceed a prednisone equivalent ≤ 10 mg/day and must be stable for at least 4 weeks prior to baseline
8. The use of concomitant methotrexate (MTX) is allowed. If using MTX, patients must have received a minimum of 3 months of therapy and be on a stable dose for at least 4 weeks prior to baseline
9. Patients are considered to be in generally good health based upon the result of a medical history, physical examination, laboratory profile, chest X-ray and ECG

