### Exclusion criteria

Patients will be considered ineligible for study participation is any of the following criteria are met:

1. Patient has previously received anti-TNF therapy, or another investigational drug for psoriasis or psoriatic arthritis **in the past 2 months**
2. Patient has received any DMARD or systemic psoriasis therapy (other than MTX) within 4 weeks prior to baseline
3. Patient has received an intra-articular injection with corticosteroids within 4 weeks prior to baseline
4. Patient has an active skin or connective tissue disease (other than psoriasis and psoriatic arthritis) that would interfere with the assessment of either psoriasis or arthritis
5. Patient has received topical psoriasis therapy (e.g. corticosteroids, vitamin D analogues, keratolytics, coal tar or topical retinoids) within 2 weeks prior to baseline

NB: low potency topical steroids to be used for scalp, palms, groin and/or soles of feet only are allowed

1. Patients has a history of active tuberculosis. A PPD test and chest X-ray done at screening should be negative (in case of latent tuberculosis, a patient may enter the study if prophylaxis with isoniazide is begun prior to administration of adalimumab)
2. Patients has a recent history of (or persistent) infection requiring hospitalization or antibiotic treatment within 4 weeks of baseline
3. Patient is HIV positive. A HIV test done at screening has to be negative
4. Patient has evidence of a hepatitis B or hepatitis C virus infection. A serologic test for HBV and HCV done at screening has to be negative
5. Patient has a significant history of cardiac, renal, neurological, metabolic or any other disease that may affect his/her participation in this study
6. Patient has a history of malignancy (other than basal cell carcinoma of the skin) in the past 10 years
7. If female, patient should not be pregnant or breast-feeding. A serum pregnancy-test will be performed at screening has to be negative
8. Patient is, in the opinion of the investigator, unable to comply with the requirements of the study protocol or is unsuitable for the study for any reason

Any patient who does fulfill the inclusion criteria at screening, but not at baseline may be screened again, and if inclusion criteria are met, enter the study.

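### The in-study exemption for topical psoriasis treatment is looser than the entry rule it refers to, so topicals washed out before baseline may be restarted at four body sites during the randomised period

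*Protocol*

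**What the plan says.** Two places in section 3 of the protocol deal with topical psoriasis treatment.

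- **Exclusion criteria, fifth item.** A patient is ineligible if "Patient has received topical psoriasis therapy (e.g. corticosteroids, vitamin D analogues, keratolytics, coal tar or topical retinoids) within 2 weeks prior to baseline". A note beneath gives one exemption: "low potency topical steroids to be used for scalp, palms, groin and/or soles of feet only are allowed".
- **Concomitant treatment.** A list of treatments "not permitted during this study (see exclusion criteria") includes "topical corticosteroids, vit.D analogues, topical retinoids, keratolytics or coal tar (other than on the scalp, palms, groin, and/or soles of feet").

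The Concomitant treatment section also gives general advice on steroids: "It is important that steroid treatment be kept to a minimum", and "Changes of NSAIDs and increases in steroid therapy (drug or dosing) should be avoided". If there is a clear reason for such a change, it may be made and must be documented. Permitted treatments are allowed "provided that the patients have received a stable dose for at least 28 days before entering the study", but that list contains only NSAIDs, oral corticosteroids and methotrexate.

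**The concern.** The washout is there so that skin assessments from baseline on reflect study drug and not a topical product. The in-study exemption names the same four sites as the entry exemption but drops both of its limits: steroids only, and low potency only. An investigator who follows the in-study text literally can let a patient resume, at those sites, the product that had to be stopped to enter the study.

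At stake are the skin variables. PASI and BSA are scored at every visit, so the week-4 scores could include a response to a topical. The skin histology could be affected too, if the target lesion lies at one of the four sites and is treated. The Efficacy variables section lists all of these as secondary. Skin tissue is not marginal, however: the primary objective names skin inflammation alongside synovial inflammation.

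**Working it through.** The protocol states no figure on this point, so the check is a comparison of text.

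**Step 1. The two rules side by side.**

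| | Exclusion criteria, fifth item and note | Concomitant treatment, prohibited list |
|---|---|---|
| Period | 2 weeks before baseline | During the study |
| Products covered | Topical psoriasis therapy, with five classes given as examples | The same five classes, listed outright |
| Exempt sites | Scalp, palms, groin, soles | Scalp, palms, groin, soles |
| Exempt products | Steroids only | Every listed class |
| Potency limit | Low potency | None |
| Stable-use condition | None | None |

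The sites match and the exempt products do not. A potent steroid, vitamin D analogue, retinoid, keratolytic or coal tar on the scalp is barred before baseline and allowed afterwards.

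**Step 2. Does other text close the gap?**

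- The pointer to the exclusion criteria suggests that the narrow exemption was meant. It sets no order of precedence, and the item beneath it states the wider exemption outright.
- The steroid advice discourages moving to a stronger steroid but allows it for a documented reason. It covers one of the five classes and is silent on the other 5 - 1 = 4.
- The 28-day stable-dose condition does not extend to topicals. Copying the entry note alone would therefore still let a patient start a low-potency steroid after baseline.
- The Liability and insurance section makes cover conditional on the investigator's consent to other medical treatment. That may restrain patients, but it does not tell the investigator which topicals to refuse.

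**Step 3. Can topical use reach the endpoints?**

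- The PASI form (Appendix 5) scores head, upper limbs, trunk and lower limbs, with no carve-out for the exempt sites. No carve-out is given for BSA either.
- The Design section asks for one target lesion, preferably sun-protected. The Secondary efficacy variables text asks for the edge of an active lesion, and the same lesion at week 4. Neither says that the lesion must stay untreated.
- Synovial biopsies come from an inflamed knee, wrist or ankle. Topicals on the scalp, palms, groin or soles do not bear on them.

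**Step 4. What can be said about size?** Let p be the proportion of an arm that starts a topical and d the mean change it causes among those patients. The shift in the between-arm difference is p(adalimumab) x d(adalimumab) - p(placebo) x d(placebo). The protocol gives none of the four terms. The shift is zero if use and effect are equal in the two arms. In that case the change within each arm, which the Statistical methods section also plans to describe, would still contain p x d. Only patients with lesions at the four sites can contribute, and some patients may have no active lesions at all, since entry requires "Patients have presence of active cutaneous lesions of psoriasis or documented history of psoriasis diagnosed by a dermatologist".

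**The case against.** The strongest reply is that nothing here conflicts. One rule governs the 2 weeks before baseline and the other the study itself, so a patient can comply with both. The in-study parenthesis also reads naturally as a shortened repeat of the entry note: same four sites, under a heading that refers to the exclusion criteria, with steroid advice pointing the same way. Use must be recorded in the case record form, the 4-week period is randomised and double-blind, and no harm has been shown.

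Much of this stands. A reader might infer that the protocol contradicts itself; it does not, because the periods differ. The narrow rule was probably intended, and loose drafting is the likely cause. A reader might also infer a bias for or against adalimumab. The documents support neither: patients whose skin does not improve may be likelier to start a topical, but that is conjecture without a documented rate.

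What does not stand is that the text settles the matter. Nothing says that the exemption is meant to widen after baseline, and nothing stops an investigator from following the wider wording. Recording use allows it to be described afterwards, not undone.

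**Conclusion.** The point holds as a minor one: the in-study exemption is looser than the entry exemption to which it refers. Followed literally, it lets a washed-out topical be restarted at four sites during the 4-week randomised period. The consequence is limited to PASI, BSA and possibly lesional histology. Its size and direction are unknown.

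This rests on two assumptions: that investigators may apply the in-study text as written, and that some patients have treatable lesions at the four sites. With 24 patients randomised 1:1, or 24 / 2 = 12 per arm if allocation is even, a few such patients would carry weight in the skin results. The protocol does not allow their number to be estimated.

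Two stronger readings go too far. A reader might infer that the synovial results are compromised; they are not affected. A reader might also infer that lesions at the four sites should be barred from biopsy. The text does not require that, and it could cost skin biopsies in a small study that already admits patients with only a history of psoriasis.

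**What to change.** Make two changes of wording.

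1. In Concomitant treatment, narrow the parenthesis so that the only exempt topicals are low-potency steroids on the scalp, palms, groin and soles, with use unchanged from baseline through week 4. The stability condition is needed because neither existing rule has one.
2. In Design, state that the biopsied target lesion receives no topical treatment until the week-4 biopsy. The choice of lesion site can stay as it is.

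The cost is slightly less topical relief at those sites for 4 weeks. Visits, sample size and analysis do not change.

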## **Adverse events**

An adverse event is defined as any untoward medical occurrence in a clinical investigation subject administered a pharmaceutical product. The term adverse event does not imply a causal re­lation­ship with the study treat­ment.

The period of observation for adverse events extends from the time the patient gives informed consent until he or she undergoes the final exami­nation as part of the study. Adverse events occurring after this period should also be mentioned in the CRF, if the adverse event comes to the knowledge of the investigator.

All adverse events ‑ whether considered as­soci­ated with the use of the study medication or not ‑ must be followed to a satisfactory conclusion, i.e. until they return to baseline, become stabilized or until there is a satis­factory explanation for the changes ob­served. In case of death a full pathologist's re­port should be supplied, if possible. All findings must be reported in the case record form and in the patient's medi­cal re­cords.

### Adverse event severity and reporting

An adverse event is considered a serious adverse event (SAE) if it meets the following criteria:

- any event that is fatal or life‑threatening
- any event that is permanently or significantly disabling
- any event that requires or prolongs hospitalization
- any event that involves cancer or congenital anomaly
- any event that occurs with overdose (any dosage higher than that recommended in the Investigator's Brochure or package insert)
- any event that suggests a significant hazard

All serious adverse events which occur during the period of observation MUST be re­ported within 24 hours or at the latest on the following working day by tele­phone and/or telefax to the sponsor, whether consid­ered to be associated with the study medication or not. The event will be docu­mented in the CRF, as complete as possible. If considered necessary, the inves­tigator will also in­form the local medical ethics committee and authorities.

Any adverse events considered not to be a serious adverse event, should be documented in the CRF.

Regardless of the classification of an adverse event as serious (see above), the severity of all adverse events must be assessed as mild, moderate or se­vere.

*severe* the adverse event causes considerable interference with the subject’s usual activities and may be incapacitating or life-threatening

*moderate* the adverse event causes the subject discomfort and interrupts the subject’s usual activities

*mild* the adverse event is transient and easily tolerated by the subject

Furthermore, the investigator will assess the relationship of the adverse event to the use of the study drug into:

*not related* adverse event is due to an underlying or intercurrent illness or effect of another drug and is not related to the study drug

*probably not related* adverse event has little temporal relationship to study drug and a more likely etiology of the adverse event exists

*possibly related* adverse event has a strong temporal relationship to the study drug and an alternative etiology is less likely

*probably related* adverse event has a strong temporal relationship to the study drug or recurs on re-challenge and another etiology is unlikely

If in the opinion of the investigator the adverse event is considered (probably) not related, an alternative etiology must be provided.

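### The adverse-event causality grades are not exhaustive: *possibly related* needs the same strong timing as *probably related*, so some foreseeable events have no valid grade

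*Protocol*

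**What the plan says.** The protocol (section 3, Adverse event severity and reporting) defines four grades:

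- The lowest grade, *not related*, is worded as "adverse event is due to an underlying or intercurrent illness or effect of another drug and is not related to the study drug". It has no timing criterion.
- The second, *probably not related*, applies under this definition: "adverse event has little temporal relationship to study drug and a more likely etiology of the adverse event exists". Both conditions must hold together.
- The third, *possibly related*, is given as "adverse event has a strong temporal relationship to the study drug and an alternative etiology is less likely". Again there are two joint conditions.
- The highest, *probably related*, reads "adverse event has a strong temporal relationship to the study drug or recurs on re-challenge and another etiology is unlikely". This is the only grade that mentions re-challenge.

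For either of the two unrelated grades the investigator must name another cause. There is no grade for an event that cannot be assessed.

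The same section requires serious adverse events to be reported whether or not they are considered "to be associated with the study medication or not", and all non-serious events to be entered in the CRF. The Adverse events section requires every adverse event to be followed to a satisfactory conclusion, whatever its presumed cause. The Clinical variables part of the safety section sets a condition: "Any evaluations that are abnormal and considered to be related to the study medication will be followed until they return to baseline". Follow-up there may also end once the finding is thought to lack clinical significance.

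**The concern.** A causality scale should give each event exactly one grade. Here the step from *probably not* to *possibly* changes two things at once: timing goes from little to strong, and the other cause goes from more likely to less likely. Events that change on only one of these, or that lie between the levels, have no place. The step from *possibly* to *probably* does not raise the timing requirement at all.

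Such events are foreseeable in this trial. Injections are given every other week, so an event between scheduled doses falls within about 14 days of one, and its timing will seldom be clearly little. Competing causes are part of the design: methotrexate, NSAIDs and low-dose corticosteroids are allowed, and patients undergo arthroscopies and skin biopsies. Liver enzymes are safety variables measured at all four visits.

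Two things are at stake. One is the consistency of a drug-relatedness summary in 24 patients, where regrading one or two events is visible. The other is the follow-up of abnormal evaluations, which the Clinical variables text ties to a judgement of relatedness.

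**Working it through.** The plan states no figure on this point, so there is none to reproduce. The check lists the combinations and applies the definitions literally.

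**Inputs**, all from Adverse event severity and reporting:
- Timing levels named: strong, little (2).
- Levels of the other cause named: more likely, less likely, unlikely (3), treated as distinct.
- Combinations: 2 × 3 = 6.

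*Not related* is kept outside the grid because it states a conclusion and has no criteria. Re-challenge is assumed not to have occurred.

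The definition of *probably related* joins its conditions with *or* and *and* without grouping them. Reading A is (strong timing or re-challenge) and another cause unlikely. Reading B is strong timing alone, or (re-challenge and another cause unlikely).

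| Timing | Other cause | Reading A | Reading B |
|---|---|---|---|
| strong | more likely | none | probably |
| strong | less likely | possibly | possibly and probably |
| strong | unlikely | probably | probably |
| little | more likely | probably not | probably not |
| little | less likely | none | none |
| little | unlikely | none | none |

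Reading A: 6 − 3 = 3 of 6 unmatched. Reading B: 6 − 4 = 2 of 6 unmatched, and one combination falls in two grades.

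**Sensitivity to levels the protocol does not name** (total minus matched = unmatched):

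| Levels added | Reading A | Reading B |
|---|---|---|
| Equally likely cause | 8 − 3 = 5 of 8 | 8 − 5 = 3 of 8 |
| Moderate timing | 9 − 3 = 6 of 9 | 9 − 4 = 5 of 9 |
| Both | 12 − 3 = 9 of 12 | 12 − 5 = 7 of 12 |

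**A worked case.** ALAT is raised shortly after an injection in a patient on methotrexate, and both drugs are equally plausible causes. Timing is not little, so the event is not *probably not related*. The other cause is not less likely, so it is not *possibly related*. *Not related* needs a firm attribution that the investigator cannot make. Under reading A no grade is left. Under reading B the event becomes *probably related* on timing alone, although the other cause is just as likely.

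**The follow-up texts side by side.** Clinical variables provides for follow-up of abnormal evaluations considered related. Adverse events requires follow-up of all adverse events, related or not. Where an abnormal evaluation is also an adverse event, the two state different conditions.

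**The case against.** The strongest case against is that little in this protocol turns on the grade. Serious events are reported, non-serious events recorded and adverse events followed regardless of causality. No count of related events is an endpoint. Grading in the 4-week randomized period is double-blind, so loose definitions apply to both arms. All of this stands, and it limits the harm.

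Four stronger readings are tempting, and the document does not support them.

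- A reader might infer that most combinations lack a grade. On the protocol's own terms it is half, or a third under reading B. A majority appears only when levels that the protocol does not name are added. *Not related* can also take a well-timed event with a more likely cause, if the investigator firmly attributes it elsewhere.
- A reader might infer that related events will be under-counted. Both unrelated grades require a named other cause, so a weakly timed event with no better explanation is hard to place there and may be pushed up. Some events may go down and others up.
- A reader might infer that follow-up will be cut short. The Clinical variables text does not say that unrelated findings are dropped, and any finding that is an adverse event falls under the general rule. What is shown is an inconsistency to settle.
- A reader might take the requirement to "practice a reliable method of birth control until 150 days post-study" as evidence that weakly timed drug effects are expected. It is a contraception precaution and says nothing about how adverse-event timing is judged.

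**Conclusion.** The point holds as a defect in the stated definitions. *Possibly related* and *probably related* share one timing threshold, *probably not related* requires two conditions together, and the result is 3 of 6 combinations without a criterion-based grade (2 of 6 under reading B, with one overlap). Neither reading gives a clean scale. The count assumes that the three levels of other cause are distinct and that re-challenge has not occurred.

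Inconsistent grading of events with competing causes or intermediate timing is the supportable consequence. Missing some drug-related events is a risk. The number of events and the net direction cannot be computed from the document. The effect is confined to how events are graded in a 24-patient safety report and to which abnormal evaluations fall under the Clinical variables follow-up sentence. The tissue comparisons are untouched.

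**What to change.** Reword the grades so that each event has exactly one:

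- *Not related*: unchanged.
- *Probably not related*: a more likely cause exists, whatever the timing, and the event does not meet *not related*.
- *Probably related*: (strong timing or recurrence on re-challenge) and another cause unlikely, with the grouping made explicit.
- *Possibly related*: every remaining event, that is, one whose other cause is equally likely, less likely or not identified and which does not meet *probably related*.

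On the grid of 2 timings × 4 levels of other cause (equally likely included, no re-challenge), this places 2 combinations in *probably not*, 1 in *probably* and 5 in *possibly*: 2 + 1 + 5 = 8 of 8, with no overlap. Intermediate timing also has a place, because timing now matters only for *probably related*. The rule that unrelated grades need a named cause fits unchanged.

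The follow-up statements in Clinical variables and in Adverse events must also be reconciled. Which rule applies is for the sponsor and the investigator to decide.

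The cost is a few lines of protocol wording and matching CRF text. No dose, visit or sample changes. The small downside is that more events will be listed as possibly related.
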